### Blinding

Outcome measures will be collected by recovery unit medical and nursing staff that are blinded to the participants’ treatment allocation. The interventions will be delivered by separate groups of operative staff (operative donor team), and each group will be blinded to the treatment delivered by the other. The trial will adhere to procedures to maintain separation between the data management staff who will record the outcome data and the donor operative nursing and medical staff who will deliver the intervention(s).

### Data collection

The data from patients enrolled in the Simvalt study are collected by EDC (electronic data capture) using a web-based eCRF. The link to access to eCRF is https://simvalt.fullcro.org, the data, once entered in eCRF, are stored in a database. The credentials (user name and password) to access to eCRF are given individually to each user upon request of the Sponsor, after the request the credentials are provided within 1 working day; the password respects the security requirements (it must have at least one capital letter, one number, one special character and it must be composed of at least ten digits). The patient data are anonymized; it means that each patient is identified with a code which is automatically generated by the eCRF at the moment of enrolment, in the eCRF only the year of birth and the gender of patient is collected, no other personal data (name, initials, complete date of birth) are collected, so only the Investigator at the site can know the identity of the patient.

Collection of laboratory evaluations, and storage of biological specimens (liver biopsies) for genetic or molecular analysis in the current trial and for future use in ancillary studies, will be stored at ISMETT.

#### Statistical analysis

Intention-to-treat analysis will be applied. Quantitative variables will be compared with the Student t-test or the Wilcoxon rank-sum test and categorical variables will be compared with the chi-squared test or Fisher’s exact test as appropriate. No a-priori criteria will be set for an early end of the study. Data will be analyzed according to the 2 × 2 randomized factorial study design. All of the phases will follow the Consolidated Standards of Reporting Trials 2010 Statement to improve the reporting of parallel-group randomized controlled trial, enabling readers to understand the trial’s design, conduct, analysis. and interpretation as well as to assess the validity of its results. It will be achieved through complete transparency from study investigators. All analyses and graphics were performed in the R statistical computing environment, version 3.4.3.

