### Donor shortage

LT is the only life-saving therapy for most types of end-stage liver disease. In Italy, the overall rate of cadaver donation is 22.2 donors per million per year, and in some regions, like Sicily, the rate is 12.6 donors per million per year. In the past few years, IRCCS-ISMETT, a transplant hospital in Sicily, has been committed to counteracting this organ shortage. Over the years, the number of transplants has steadily increased thanks to marginal donors, living donors, and split LT. ISMETT has implemented techniques and strategies to most efficiently use valuable resources in order to maintain a high level of LT. From July 1999 till May 2014, we performed 902 LTs for adults: 755 (84%) were performed by using 601 whole livers (80%), 99 (13%) were living-related LTs, and 55 (7%) were split LTs. The one-year survival rate (cadaveric liver transplantation) is 85.4%. [12–14]

The shortage of organs led to the use of steatotic liver grafts from extended-criteria deceased brain donors (DBDs), even though these livers are more susceptible to I/R injury and have poorer outcomes than non-steatotic livers. Preclinical studies have demonstrated that the negative effects of I/R can be prevented by adding Simvastatin to the cold preservation solution shortly before procurement to protect both parenchymal and endothelial components of the liver after warm reperfusion.

The proposed project aims to be the first prospective randomized clinical trial to prove the efficacy of Simvastatin in preventing I/R injury and expand the donor pool.

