### Outcomes

The primary outcome measure in this trial is postoperative graft survival after LT. The secondary outcomes of interest are patient survival, hospitalization stays, and all transplant-related complications in terms of the multi-tier Clavien grading system after LT. The grading system is used in order to identify a significant relation into two homogenous groups of liver transplanted patients, which only differ for Simvastatin or non-administration regimen utilizing the same procedure, with identical surgical instruments, and medical and nursing skilled staff. Baseline data on graft function and patient performance status will be collected immediately prior to discharge from the recovery unit (T0). Follow-up measures will be collected at three time points**:** 3-month (T1), 6-month (T2) and 12-month (T3)**,** after LT (see Fig. 1). All participants will be routinely evaluated with a post-reperfusion liver biopsy (sample), intensive care monitoring, daily laboratory and ultrasound examinations for the first week after the operation and when required during their hospital stay.

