### Sample size

We hypothesize that Simvastatin’s protective effects may occur in the liver during the harvesting procedure from the deceased donor and could significantly ameliorate post-LT outcomes. To reach the above-mentioned goals, we decided to recruit 106 patients. This sample size achieves 90% power to detect a difference of 14.6% between the two groups survival using a one-sided binomial test. The target significance level is 0.05. These results assume a null hypothesis that the proportion of the group with the standard procedure is 0.85.

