## Discussion

This trial is the first to rigorously evaluate the effect of preoperative DBD treatment with the administration of Simvastatin on LT outcomes. The use of Simvastatin could reduce donor liver damage and decrease the length of hospital stay and the rate of complications. There is a remote probability of liver damage with the use of statins. However, Simvastatin is a well-known drug with a minimal reported risk of liver damage compared with the other statins. The factorial design of the trial enables a head-to-head comparison of the individual and cumulative effects of this intervention, which should provide valuable evidence to inform clinical practice.

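### Hospital stay is compared by t-test or Wilcoxon test with no separate treatment of stays ended by death, so early in-hospital deaths would enter as short stays and bias the comparison against a drug that prevents them

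*Protocol article*

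**What the plan says.** In the protocol article, Outcomes lists hospital stay among the secondary endpoints: "The secondary outcomes of interest are patient survival, hospitalization stays, and all transplant-related complications". Purpose lists it too. The Discussion treats a shorter stay as a hoped-for benefit, saying that the drug could "decrease the length of hospital stay and the rate of complications".

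The method is in Statistical analysis: "Intention-to-treat analysis will be applied", and "Quantitative variables will be compared with the Student t-test or the Wilcoxon rank-sum test". Hospital stay is a quantitative variable, so it falls under this rule, and no other method is named for it. The article does not say what value a patient who dies before discharge receives. Patient survival is a separate secondary outcome.

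**The concern.** Length of stay is cut short by death. Under intention to treat the patients who die remain in the comparison. If their stay is entered at its observed length, a death on day 5 ranks as a better result than most discharges alive.

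This matters because the trial is built on the hope of fewer losses in the simvastatin arm. If the drug prevents early deaths, those deaths fall mainly in the control arm and shorten its stays, so the drug is penalised for working. If the drug caused early deaths, the same mechanism would flatter it. Since the article presents shorter stay as a possible benefit, this comparison may carry a claim in the final report.

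**Working it through.** **Arm size.** The article gives no figure for hospital stay, so only the sample size can be reproduced. Sample size states "we decided to recruit 106 patients" for 0.85 v 0.996 (a 14.6-point difference), one-sided alpha 0.05 and 90% power. The unpooled formula gives

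n = (1.645 + 1.282)² × [0.85×0.15 + 0.996×0.004] / 0.146² = 8.564 × 0.1315 / 0.02132 = 52.8,

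that is 53 per arm and 106 in total. The allocation ratio is not stated, but 1:1 reproduces the total, so 53 per arm is used below.

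**Assumptions not in the article.** Survivors' stay is log-normal with log-SD 0.6 and median 15 or 18 days. Time to in-hospital death is exponential. In-hospital death rates are as listed. The test is a two-sided 5% Wilcoxon test, so 2.5% lies in each direction.

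**Direction of the bias.** Let d_C and d_T be the in-hospital death proportions (control, simvastatin), and q the probability that a survivor's stay exceeds a time to death. If the drug has no effect on survivors' stay and deaths enter at observed length, summing over the four pairings of survivor and death gives

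P(drug stay > control stay) = ½ + (d_C − d_T)(q − ½).

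With fewer deaths on the drug, the bias is against it only while q is above ½, that is, while deaths mostly precede discharge. For 10% v 2% and a median stay of 15 days:

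| Median time to death | q | Formula | Simulated |
|---|---|---|---|
| 3 days | 0.93 | ½ + 0.08×0.43 = 0.534 | 0.534 |
| 7 days | 0.75 | ½ + 0.08×0.25 = 0.520 | 0.520 |
| 15 days | 0.51 | ½ + 0.08×0.01 = 0.501 | 0.502 |
| 25 days | 0.37 | ½ − 0.08×0.13 = 0.490 | 0.489 |

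The penalty disappears at about 15 days and reverses by 25.

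**Wrong-direction significance with no true effect on stay.** The null standard error of the Wilcoxon proportion is √[(2n+1)/(12n²)] = √(107/33,708) = 0.0563. With a median stay of 15 days and a median time to death of 7 days:

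- 5% v 0%: proportion 0.513; 0.013/0.0563 = 0.23; P(Z > 1.96 − 0.23) = 4.2%. Simulated 4.2%, mean stay 0.4 days longer on the drug.
- 10% v 2%: 0.020/0.0563 = 0.36; P(Z > 1.60) = 5.5%. Simulated 5.4%, 0.65 days longer.
- 15% v 0.4% (extreme): 0.036/0.0563 = 0.64; P(Z > 1.32) = 9.3%. Simulated 9.0%, 1.2 days longer.

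With a median stay of 18 days, deaths from 5% v 0% to 10% v 2% and a median time to death of 5 to 10 days, simulation gives roughly 3.5-8%. At a median time to death of 20 days there is no penalty.

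**Power when survivors' stay is truly shorter.** The benchmark is the case with no deaths. For a 25% shorter stay, P(drug > control) = Φ(ln 0.75 / (0.6√2)) = Φ(−0.339) = 0.367, and power is Φ((0.5 − 0.367)/0.0563 − 1.96) = Φ(0.40), about 66%. With deaths entered at observed length (median stay 18 days, same death rates, median time to death 5 to 10 days) simulated power is about 39-57%.

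For a 20% shorter stay the same formula gives Φ(−0.263) = 0.396 and power Φ(0.104/0.0563 − 1.96) = Φ(−0.11), about 45%. With a median stay of 15 days and a median time to death of 7 days, simulated power is 35% at 5% v 0%, 32% at 8% v 2% and 28% at 10% v 2%. Ranking deaths worst gives 60%, 60% and 65%, which is above the no-deaths benchmark because the survival benefit is then counted too.

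**The case against.** The strongest reply is that this is an unstated detail and not an error. The rule for quantitative variables is generic, it does not mention hospital stay, and the scoring of deaths in a secondary outcome often sits in the full protocol or analysis plan, neither of which is shown. The Wilcoxon test is compatible with ranking deaths worst. This stands in part: a reader might infer that the article tells the analyst to count deaths as short stays, and it does not say so. But the article does name the tests and does keep all randomised patients, and nothing in it separates death from discharge. The t-test option has no natural score for a death at all. Followed as written, the rule gives the result described.

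A reader might also infer that the comparison is always biased against simvastatin. The working shows that the direction depends on when deaths occur, and the article gives no timing.

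A third tempting step is to carry the 14.6-point difference or the centre's 85.4% one-year survival over to in-hospital mortality. The first concerns the primary survival comparison, on graft survival at 3, 6 and 12 months; the second is a one-year rate. Losing a graft is not dying, and a survivor of graft loss may stay longer.

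Finally, under one set of assumptions (median stay 20 days, deaths on days 2 to 15, 3-10% v 0-0.4%, stay 25% shorter) worst-rank power is 72-86%. That should not be read as stay information recovered, because it includes the survival benefit.

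It also counts against the point's weight that patient survival is reported separately, so an imbalance in deaths would be visible beside the stay result. That does not correct the stay comparison or its p-value.

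**Conclusion.** The concern holds in a limited form. With the tests as named, under intention to treat and with no separate treatment of death, the hospital-stay comparison mixes stay with death. It is biased against a drug that prevents early in-hospital deaths, and the bias fades or reverses if deaths come at or after the typical discharge time. A significant or null result on stay could not be read clearly either way.

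The size is modest: under the assumed early-death scenarios the wrong-direction error is a few points above 2.5%, and 9 to 27 points of power are lost for a 25% shorter stay (66 − 57 and 66 − 39). These figures rest on assumed mortality, death timing, stay distribution, 1:1 allocation and a two-sided test, so they illustrate and do not predict. Only a secondary outcome is affected; the primary graft-survival comparison is untouched. The change is worth making. If the full protocol or analysis plan already has a rule for in-hospital deaths, the point is closed by citing it.

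**What to change.** Before unblinding, state that hospital stay is compared by a Wilcoxon rank-sum test with in-hospital deaths assigned the worst rank, and not by t-test. An acceptable alternative is time to discharge alive with death as a competing event. Report median stay among survivors as a description only, beside the number of in-hospital deaths in each arm.

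The cost is one sentence in Statistical analysis and no new data, since stay and patient survival are already outcomes. The downside is small: the worst-rank result is a composite of stay and death, should be labelled as such, and is less easily expressed in days. Settling the rule beforehand also removes the option of choosing the handling of deaths once the results by arm are known.

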### Monitoring

Circumstances under which unblinding is permissible are related to severe and not expectable adverse recipient reaction to Simvastatin or Placebo, and PI will be involved procedure for revealing a participant’s allocated intervention during the trial. Outcome measures will be collected by recovery unit medical and nursing staff that are blinded to the participants’ treatment allocation. The interventions will be delivered by separate groups of operative staff (operative donor team), and each group will be blinded to the treatment delivered by the other. The trial will adhere to procedures to maintain separation between the data management staff who will record the outcome data and the donor operative nursing and medical staff who will deliver the intervention(s). In addition, DSMB will review the following items: 1) interim/cumulative data for evidence of study-related adverse events; 2) data quality, completeness, and timeliness; 3) adequacy of compliance with goals for recruitment and retention; 4) adherence to the protocol; 5) factors that might affect the study outcome or compromise the confidentiality of the trial data.

DSMB will provide official communications that will occur between EC and IRB, including: 1) modifications of the study protocol based upon the review of the safety data; 2) suspension or early termination of the study because of serious concerns about subjects¿ safety, inadequate performance or rate of enrolment or because study objectives have not been obtained according to pre-established statistical guidelines; 3) optional approaches for clinicians and study investigators to consider when the DSMB determines that the incidence of primary study outcomes is substantially less than expected.

### Ethical considerations

The project has been approved by the hospital’s human research ethics committee. Informed consent will be obtained from all participants. ISMETT PI and co-investigators will obtain informed consent or assent from potential trial participants or authorized surrogates, during outpatient clinic visits in waiting-list time and during the ISMETT admission date for liver transplantation.

## Discussion

This trial is the first to rigorously evaluate the effect of preoperative DBD treatment with the administration of Simvastatin on LT outcomes. The use of Simvastatin could reduce donor liver damage and decrease the length of hospital stay and the rate of complications. There is a remote probability of liver damage with the use of statins. However, Simvastatin is a well-known drug with a minimal reported risk of liver damage compared with the other statins. The factorial design of the trial enables a head-to-head comparison of the individual and cumulative effects of this intervention, which should provide valuable evidence to inform clinical practice.

### Trial status

The proposed trial has been validated and accepted for financial support by the Italian National Health Ministry (Programme of “Ricerca Finalizzata 2013” - Clinical health care research - GR-2013-02357764). Patient inclusions have been ongoing since 30 June 2018.

## Abbreviations

DBD: Donor after brain death
DSMB: Data and safety monitoring board
HIV: Human immunodeficiency virus
HLA: Human leukocyte antigen
IMPD: Investigational medicinal product dossier
KLF2: Kruppel-like factor 2
LT: Liver transplantation
NCA: National Competent Authority
PI: Primary investigator
